#### Model specification

For each outcome variable, four two-group models reflecting four alternative hypotheses will be specified and compared. First, Model A will include for both groups a latent intercept but not a latent slope (i.e., a latent change factor), reflecting the hypothesis that scores on the outcome variable will not change from pre- to posttest for either the intervention group or the matched comparison group. Second, Model B will include a latent slope for the intervention group but not for the matched comparison group, reflecting the hypothesis that scores for the intervention group will change, but scores for the matched comparison group will not change. Third, Model C will include a latent slope for the matched comparison group but not for the intervention group, reflecting the hypothesis that scores for the matched comparison group will change, but scores for the intervention group will not change. Fourth, Model D will include latent slopes for both groups, reflecting the hypothesis that scores for both the intervention group and the matched comparison group will change. For each model, outcome variables will be modeled as latent variables with multiple indicators (either items or item parcels) to account for measurement error. Thus, latent intercepts and latent slopes will be second-order factors.

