#### Model estimation and model testing

All models will be estimated in Mplus 8.4 [43] using a robust maximum likelihood estimator and a Huber-White adjustment to the standard errors and chi square test of model fit, as implemented in Mplus’s TYPE = COMPLEX feature, to consider cluster sampling of participants within schools. Each model will be assessed with the chi square test of exact fit and its *p*-value, the comparative fit index (CFI), the Tucker-Lewis index (TLI), the root mean square error of approximation (RMSEA), and the standardized root mean square residual (SRMR). Good model fit will be indicated by: chi square *p*-value > .05, CFI > .95, TLI > .95, RMSEA < .06, and SRMR < .08 [44].

The main hypothesis will be evaluated for each outcome variable by comparing Models A-D using the Bayesian information criterion (BIC). When comparing models, lower BIC indicates better relative model fit; a BIC difference of greater than 10 indicates very strong evidence against the model with the largest BIC [45]. If Model D is selected, then the difference in change between the groups will be evaluated by constraining the mean and variance of the latent slope to be equal across groups and comparing this model with an unconstrained model using the Satorra-Bentler nested chi-square test for robust maximum likelihood. In addition, the sensitivity of each selected model to the assumption of pretest equivalence between groups will be tested by constraining the mean and variance of the latent intercept to be equal across groups and comparing this model with an unconstrained model, as suggested by [42].

To assess power for this analysis, we conducted a Monte Carlo simulation using Model D. The model included two groups (intervention and comparison), latent intercepts and slopes for both groups, and three continuous indicators (e.g., parcels) at both pretest and posttest. We specified population values of .70 for all standardized factor loadings and a mean difference of .50 between the latent slopes of the two groups. We assumed a sample size of 288, with 144 in each group. Under these assumptions and using 1,000 replications and a robust maximum likelihood estimator, the power estimate for the group difference in latent slopes was .88.

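### Models A to C express no change by omitting the whole latent slope, so the BIC choice among A to D responds to variation between families in change as well as to mean change

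*Protocol article*

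**What the plan says.** The section Model specification sets out four two-group models for each outcome. For the first, "Model A will include for both groups a latent intercept but not a latent slope (i.e., a latent change factor"). For the second, "Model B will include a latent slope for the intervention group but not for the matched comparison group". Model C is the mirror image of B, and Model D has a slope in both groups. Where a group has no slope, the article reads this as no change in that group's scores. Multiple indicators are used to remove measurement error, and the only second-order factors named are the intercept and the slope.

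The section Model estimation and model testing gives the decision rule: "The main hypothesis will be evaluated for each outcome variable by comparing Models A-D using the Bayesian information criterion (BIC"). A separate test of the group difference is planned only if Model D is chosen. It is made by "constraining the mean and variance of the latent slope to be equal across groups", so the slope has both a mean and a variance.

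The main hypothesis (Aim, design, and setting; Data analysis plan) concerns pre-to-post benefit relative to the comparison group.

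**The concern.** Benefit relative to a comparison group is a statement about mean change. Omitting a latent slope says more than that the mean change is zero. With two waves and measurement error already removed, it also says that no family changes differently from any other. If families do vary in true change, a model with a slope fits better even when the average change is nil.

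Model B matters most. It states the hypothesised pattern, and nothing further is planned to test the group difference when it is chosen. B could win because intervention families vary more in their change, or by chance when both groups vary equally.

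**Working it through.** **Inputs from the article** (Model estimation and model testing): "We assumed a sample size of 288, with 144 in each group"; "three continuous indicators (e.g., parcels) at both pretest and posttest"; "population values of .70 for all standardized factor loadings"; "a mean difference of .50 between the latent slopes of the two groups"; stated power .88. **Not given, so assumed:** slope variance s as a multiple of the pretest latent variance (range 0 to 1.0 in the selection runs), and two-sided 5% for the power figure.

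**1. The stated power.** With loading .70 the residual variance is 1 − .49 = .51. The variance of estimated latent change is about v = s + (θ1 + θ2)/(3 × .49), and power ≈ Φ(.50/√(2v/144) − 1.96).
- Residual .51 at both waves, s = 1.1: v = 1.1 + 1.02/1.47 = 1.794, SE = .158, power ≈ .89.
- Loading standardized to .70 at both waves, so θ2 = .51(1 + s), with s = .8: v = .8 + 1.428/1.47 = 1.771, SE = .157, power ≈ .89.

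So .88 is attainable with s at about 0.8 to 1.1. It concerns the slope difference within Model D and does not describe the choice among A to D.

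**2. What omission fixes.** With a slope, the latent scores are η1 = I and η2 = I + S. Without it, η2 = η1, and the latent correlation is 1. Three parameters are lost per group: slope mean, slope variance and intercept-slope covariance. BIC rewards each omission by 3 × ln(288) = 17.0 points, so enough variation in change can outweigh that reward with no mean change at all.

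**3. Selection when mean change is zero in both groups.** Lowest BIC, 500 replications, plain maximum likelihood, no clustering or missing data. With equal latent variances at the two waves, r = 1 − s/2. Simulation error is at most √(.25/500) = 2.2 percentage points.

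| s, intervention / comparison | r | A | B | C | D | A if only slope means are constrained |
|---|---|---|---|---|---|---|
| 0.1 / 0.1 | .95 / .95 | 98% | 1% | 1% | 0% | 96% |
| 0.2 / 0.2 | .90 / .90 | 90% | 6% | 3% | 1% | 96% |
| 0.3 / 0.3 | .85 / .85 | 65% | 16% | 14% | 4% | 96% |
| 0.4 / 0.4 | .80 / .80 | 32% | 25% | 24% | 19% | 96% |
| 0.6 / 0.6 | .70 / .70 | 2% | 14% | 13% | 72% | 96% |
| 1.0 / 1.0 | .50 / .50 | 0% | 0% | 0% | 100% | 97% |
| 0.4 / 0.2 | .80 / .90 | 54% | 42% | 2% | 2% | 96% |
| 0.6 / 0.2 | .70 / .90 | 14% | 82% | 1% | 4% | 96% |

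Other runs of the same design put B at 6% and 13% for r = .7, at 15% and 20% for r = .8, and at 77% and 81% for .7 versus .9. Letting same-item residuals correlate over time lowered the last case to 61% (100 replications).

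**4. Follow-up test after D.** At s = 1.0 in both groups, the joint mean-and-variance test rejects in 4.8% of datasets. At 0.6 versus 0.2, with equal (zero) means, it rejects in 46% when applied to every dataset; a test of the means alone rejects in 4%.

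**5. When the hypothesised pattern is true.** Take s = 1, zero covariance, a slope mean of .50 in the intervention group and 0 in the comparison group. As written, D is selected in 99.8% and B in 0.2% (posttest residual .51), or D in 92% and B in 8% (posttest residual 1.02). Constraining means only, B is selected in 97% and 95%.

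**The case against.** The strongest reply is that the article does not mention first-order disturbances. In Model D the three latent variances and covariance of each group are used up by the intercept variance, slope variance and their covariance, so no disturbances can be estimated. In a group without a slope, however, the intercept variance plus two disturbances are three parameters for three moments, and are identified. If they were kept free, omitting the slope would restrict only the mean. Simulated on that reading, A is selected in 94.5 to 98.5% at r = .6 to .9, and in 97.5% (B in 1%) at .7 versus .9. This stands as a condition on the finding. But the article names only an intercept and a slope at the second order, so the restrictive reading is the plain one, and the text needs correcting either way.

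A reader might infer from the table that the plan would claim benefit in nearly every null trial once r falls to .7. The article does not support that. D leads to a group test, and C is not the hypothesised pattern.

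A reader might also infer that choosing B will be reported as benefit whatever its sign. The article does not say so: B estimates a slope mean, whose size and direction can be read.

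The article also calls BIC differences above 10 very strong evidence. B beats every rival by that margin in under 1% of datasets at equal r of .7 or .8, and in 27% at .7 versus .9. That tempers how strongly a win for B would be worded, but the article does not make 10 a cut-off for selection.

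**Conclusion.** The point holds on the plain reading of Model specification, with moderate confidence, and should be fixed before outcome analysis. As written, the A-to-D comparison mixes variation in change with mean change.

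- With zero mean change, B is selected in roughly 10 to 25% of trials at r of about .7 to .8 (one run gave 6% at .7), and in about 80% at .7 versus .9.
- At r = .9 or above in both groups the effect is small.
- With slope variance near 1 in both groups, D is nearly always chosen and the follow-up test holds the error near 5%. The A-to-D step then cannot identify pattern B even when it is true.

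These sizes rest on assumed stabilities, because the documents give none, and on there being no free disturbances in groups without a slope. They do not show that the .88 power figure is wrong.

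**What to change.** In Model specification, keep the latent slope in both groups in all four models, with free variance and free intercept-slope covariance, and define the models by slope means only:

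- A: both slope means 0
- B: comparison slope mean 0, intervention mean free
- C: intervention slope mean 0, comparison mean free
- D: both slope means free

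If free disturbances were intended in groups without a slope, say so; the change is then mainly one of wording.

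The cost is a few lines of Mplus code and no new data. Model A gains four parameters, and Models B and C gain two each. Slope-variance estimates may occasionally fall near zero when stability is very high. The article reports data collection as ongoing, so the change can be recorded before outcomes are analysed.

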#### Model estimation and model testing

All models will be estimated in Mplus 8.4 [43] using a robust maximum likelihood estimator and a Huber-White adjustment to the standard errors and chi square test of model fit, as implemented in Mplus’s TYPE = COMPLEX feature, to consider cluster sampling of participants within schools. Each model will be assessed with the chi square test of exact fit and its *p*-value, the comparative fit index (CFI), the Tucker-Lewis index (TLI), the root mean square error of approximation (RMSEA), and the standardized root mean square residual (SRMR). Good model fit will be indicated by: chi square *p*-value > .05, CFI > .95, TLI > .95, RMSEA < .06, and SRMR < .08 [44].

The main hypothesis will be evaluated for each outcome variable by comparing Models A-D using the Bayesian information criterion (BIC). When comparing models, lower BIC indicates better relative model fit; a BIC difference of greater than 10 indicates very strong evidence against the model with the largest BIC [45]. If Model D is selected, then the difference in change between the groups will be evaluated by constraining the mean and variance of the latent slope to be equal across groups and comparing this model with an unconstrained model using the Satorra-Bentler nested chi-square test for robust maximum likelihood. In addition, the sensitivity of each selected model to the assumption of pretest equivalence between groups will be tested by constraining the mean and variance of the latent intercept to be equal across groups and comparing this model with an unconstrained model, as suggested by [42].

To assess power for this analysis, we conducted a Monte Carlo simulation using Model D. The model included two groups (intervention and comparison), latent intercepts and slopes for both groups, and three continuous indicators (e.g., parcels) at both pretest and posttest. We specified population values of .70 for all standardized factor loadings and a mean difference of .50 between the latent slopes of the two groups. We assumed a sample size of 288, with 144 in each group. Under these assumptions and using 1,000 replications and a robust maximum likelihood estimator, the power estimate for the group difference in latent slopes was .88.

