### Data analysis plan

The main hypothesis that participants in the Parent Web condition will exhibit intervention-related pre- to posttest benefits relative to participants in the comparison group will be evaluated using two-wave two-group latent curve models [42] for each of the outcome variables. The pretest level of each outcome will be modeled as a latent intercept, and pre- to posttest change in the outcome will be modeled as a latent slope. Group 1 will be the intervention group comprised of participants in Parent Web. Group 2 will be the matched wait-list control comparison group.

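### If Model D is selected, the group difference in change is tested by equating slope mean and slope variance jointly (2 df), so its p-value alone does not establish a difference in average benefit

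*Protocol article*

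**What the plan says.** The Data analysis plan states the main hypothesis as the expectation that Parent Web participants "will exhibit intervention-related pre- to posttest benefits relative to participants in the comparison group". For each outcome, Models A to D are first compared by BIC. Under Model estimation and model testing, the follow-up step for Model D (slopes in both groups) consists of "constraining the mean and variance of the latent slope to be equal across groups". The fit of this restricted model is then set against that of the unrestricted one, with the "Satorra-Bentler nested chi-square test for robust maximum likelihood" as the criterion. The article gives this step as its way of judging whether the groups differ in change. No test of the slope means alone is described.

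The power paragraph in the same section is presented as referring to this analysis. It assumes 144 participants per group, "three continuous indicators (e.g., parcels) at both pretest and posttest", standardized loadings of .70 and "a mean difference of .50 between the latent slopes of the two groups". It reports that "the power estimate for the group difference in latent slopes was .88". It does not give the slope variance, the alpha level or the statistic that was counted as a rejection.

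**The concern.** Benefit relative to a comparison group is a statement about average change. The described test has a different null hypothesis: equal mean **and** equal variance of change. It can reject because only the spread of change differs.

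Unequal spread is plausible here. The groups are not randomised, one has a PATHS history and the other does not, and bonus modules and completion time vary between families (Interventions section). Uneven uptake would widen the spread of change in the intervention group only.

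Models A to C leave the slope out of at least one group. Ordinary individual differences in true change in both groups therefore tend to favour Model D, so this branch may well settle many outcomes. A significant result could then be reported as a Parent Web effect when mean change is the same. The second degree of freedom also costs power for the mean difference that the study is about.

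**Working it through.** **Inputs from the article:** two equality constraints; 144 per group; three indicators per wave; loadings .70, hence residual variance 1 − .70² = .51; slope mean difference .50; stated power .88.

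**Assumed, because the article does not give them:** alpha .05 two-sided; intercept variance 1; intercept-slope covariance 0; slope variances as listed below; loadings and indicator intercepts equal over time and between groups.

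**Method.** Fit the constrained and unconstrained two-group latent change models to population moments by maximum likelihood. The difference in fit is the noncentrality λ. Power is P(χ²(df, λ) > critical value), with critical value 3.84 for 1 df and 5.99 for 2 df.

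**1. The article's own figure.** With slope variance 1 in both groups and a mean difference of .50, λ = 10.44. This gives:
- 1 df: .898
- 2 df: .832

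The 1-df value is within 2 points of the stated .88. Other choices of slope variance (.5 to 1.2), covariance and posttest residual move the 1-df power between .84 and .97, so this match depends on the unit variance.

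**2. Cost of the second degree of freedom.** If .88 is a 1-df power, λ = (1.960 + 1.175)² = 9.83. Then:
- P(χ²(1, 9.83) > 3.84) = .88
- P(χ²(2, 9.83) > 5.99) = .81

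The loss is about 7 points. Conversely, a 2-df power of .88 needs λ = 11.89, at which the 1-df power would be .93.

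**3. Rejection with identical mean change.**

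| Slope variances (assumed) | Ratio | λ, joint test | Joint test (2 df) | Mean-only test (1 df) |
|---|---|---|---|---|
| .625 / .50 | 1.25 | 0.36 | 8% | 5% |
| 1.25 / 1.00 | 1.25 | 0.68 | 11% | 5% |
| .75 / .50 | 1.5 | 1.30 | 16% | 5% |
| 1.50 / 1.00 | 1.5 | 2.40 | 26% | 5% |
| .80 / .40 | 2 | 3.48 | 37% | 5% |
| 1.00 / .50 | 2 | 4.38 | 45% | 5% |
| 2.00 / 1.00 | 2 | 7.68 | 70% | 5% |

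A simulation of 1,000 replicates at .80 / .40, with mean change −0.20 in both groups, gave 38% for the joint test and 5.4% for the mean-only test. A rougher one of 200 replicates at 2.00 / 1.00 gave 73.5% and 3%.

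These are ordinary likelihood-ratio calculations with normal data. The planned robust scaling and cluster adjustment were not reproduced.

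**The case against.** The strongest defence is that the joint test is an omnibus step inside a longer procedure. The main hypothesis is first evaluated by BIC, and unconstrained Model D estimates a slope mean in each group, so the sign and size of the mean difference will be available. An article may leave the reporting of estimates and intervals to a fuller plan. This stands in part: it would be wrong to infer that a significant result can never be read as benefit. But the article names the joint test as the way the difference in change is evaluated. Choosing Model D by BIC shows only that both groups need a slope. Looking at the sign after a joint rejection does not hold the error rate for the mean at 5%.

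A reader might also infer that the .88 is proven to belong to a different test. The documents do not support that. Only a mean difference is described, which suggests a 1-df figure, but the statistic, alpha and slope variance are unstated. Deriving λ = 9.83 already assumes 1 df, and a 2-df test with λ = 11.89 would also give .88.

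The rejection rates rest on assumed variances, and no document figure supports any particular ratio. At 1.25 the excess over 5% is small.

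Finally, a reader might carry the argument over to the pretest check, which also equates mean and variance. It does not carry over. That check concerns equivalence of non-randomised groups, which can reasonably include spread.

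**Conclusion.** The concern holds for the test of change. That the constraint has 2 df, and that a variance difference alone can cause rejection, follows from the wording and needs no assumption. How often this would happen does depend on assumptions: about 16% to 26% at a variance ratio of 1.5 and about 37% to 70% at a ratio of 2, against 5% for a mean-only test. The joint p-value alone therefore does not establish a mean benefit.

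The power mismatch is a strong inference, not a demonstrated error. If .88 is the power of the 1-df mean test, the planned joint test has about .81 at the same effect, a modest loss.

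**What to change.** - Make the test of benefit under Model D a 1-df constraint on the latent slope means, with slope variances free in each group.
- Report the signed mean difference with its 95% CI.
- Test equality of slope variances separately and present it as a description of heterogeneity in change.
- State which test, alpha and slope variance the .88 refers to. If the joint test is kept and .88 was a 1-df figure, restate it as about .81.
- Leave the pretest equivalence check as it is.

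The cost is one line of model syntax and a few sentences of text. It needs no extra data or recruitment. Data collection is reported as ongoing, so the change can be recorded before any results are described. When slope variances are equal, power for the stated hypothesis rises.

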### The Swedish PATHS® project

The Swedish PATHS trial was a cluster randomized trial conducted between April 2014 and June 2016 [2]. Briefly, the preschool edition of PATHS is a school-based, teacher implemented universal SEL intervention developed in the U.S. and designed to promote SEC in children as a foundation for improved mental health, academic success, and overall development [1]. PATHS is delivered as a curriculum by teachers and is developmentally focused on creating a caring and emotionally responsive school and classroom climate, and is grounded in theories about brain and social emotional development in children [1]. The PATHS trial assessed the short-term (pre- to posttest) effects of PATHS in an urban Swedish preschool setting. Participating children were four to five years old (N = 285; 140 PATHS intervention group; 145 wait-list control group) and were included into the cluster (k = 26 preschools; 13 interventions; 13 wait-list control) randomized trial in two waves. Over the academic school year, children that participated in PATHS evidenced improvements in working memory and prosocial play but also showed higher occurrence of teacher-rated hyperactive behaviors compared to children in the control group. Additionally, girls in the PATHS group showed improvements in emotional knowledge and reduced anxiety relative girls in the control group [2]. Other research has examined PATHS- related outcomes in the original trial in terms of outcome moderation by income level of neighborhoods in which preschools were located [12].

In the upcoming study, the participants are the parents of the PATHS cohort children and will be recruited to the immediate intervention condition of the PW trial, with the goal to examine the effects of a universal edition of PW. The wider motivation for the upcoming study is to increase our understanding of how universally provided SEL during early childhood can be coupled with universally provided parent training programs in early adolescence to support families with children and adolescents across important developmental and transitional periods (i.e., from early childhood through early adolescence).

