### Target population and sample size

The target population for this study is the parent(s) of the 144 children (now 11–13 years old) that participated in the Swedish PATHS project (i.e., immediate intervention group) along with the parent(s) of a matched sample of 144 children (i.e., comparison group) for a total sample size of 288 families. Inclusion criteria is that the child took part in the Swedish PATHS intervention trial and their parents consented to have future contact with the PATHS research group and that the child and participating parents presently live in Sweden.

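### The stated power of .88 needs every family in a closed PATHS cohort to be analysed, on an unexplained count of 144, and the simulation as described has no clustering

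*Protocol article*

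**What the plan says.** Under Model estimation and model testing, the protocol article reports a Monte Carlo simulation of Model D. Its stated inputs are:

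- Sample size: "We assumed a sample size of 288, with 144 in each group".
- Parameters: "We specified population values of .70 for all standardized factor loadings and a mean difference of .50 between the latent slopes of the two groups".
- Measurement: "three continuous indicators (e.g., parcels) at both pretest and posttest".
- Method and result: "Under these assumptions and using 1,000 replications and a robust maximum likelihood estimator", "the power estimate for the group difference in latent slopes was .88".

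The same subsection says the outcome models will use TYPE = COMPLEX because participants are clustered within schools.

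Target population and sample size describes the PATHS side as the parents of 144 participating children, and adds "a matched sample of 144 children (i.e., comparison group) for a total sample size of 288 families". Families qualify only if "their parents consented to have future contact with the PATHS research group" and if child and participating parents now live in Sweden. Recruitment provides for telephone or text follow-up of families who do not answer the letter. The ethics section requires informed consent from every participant. The Parent-web (treatment) group subsection places the T2 survey after the parent has finished the programme.

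The Swedish PATHS® project subsection gives the size of the original trial: "N = 285; 140 PATHS intervention group; 145 wait-list control group".

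**The concern.** The number in the power calculation and the number in the target population are the same. The .88 is therefore the power if every PATHS family is eligible, consents and contributes information on change. The article's own recruitment text describes several steps at which families can be lost, and the PATHS cohort cannot be enlarged.

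Two further points affect the same sentence. The 144 equals neither arm of the original trial, so it is not clear which children form the intervention group. And the simulation description lists groups, indicators, loadings, slope difference, sample size, replications and estimator, but no clusters, although the planned analysis allows for them.

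At stake is how a null result would be read. With a published power of .88, it would count as fairly strong evidence against a slope difference of .50. With fewer families it carries less weight, and readers would have no figure telling them how much less.

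**Working it through.** **Inputs from the article.** 144 per group; slope difference .50; standardized loadings .70; three indicators per wave; power .88; original arms of 140 and 145; 13 intervention preschools.

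**Assumptions.** Two-sided alpha of .05, and all participation levels and ICCs below. The article gives no alpha for the simulation, no latent slope variance, no participation or attrition rate, and no ICC.

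**1. The stated figure.** It cannot be reproduced strictly, because the slope variance and the intercept–slope covariance are not given. The expected-information power of a two-group second-order change model, with 144 complete and independent families per group, runs from about .79 to .99 for slope variances of 1.2 down to .2. Slope variance 1 with unit factor variance at both waves gives .897. So .88 is compatible with full numbers and no clustering, but it depends on an unstated SD.

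**2. Calibration to .88.**

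- z(.975) + z(.88) = 1.960 + 1.175 = 3.135.
- Implied SE = .50 / 3.135 = .1595.
- Implied SD of change = .1595 × √(144/2) = 1.353, variance 1.83.
- Measurement error contributes 2 × .51 / (3 × .49) = .69, leaving a latent slope variance of about 1.14.

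This is calibration, not verification.

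**3. Fewer families.** SE = 1.353 × √(1/n₁ + 1/n₂), power = Φ(.50/SE − 1.96), and the difference detectable with 80% power = (1.960 + .842) × SE = 2.80 × SE.

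| PATHS families | Both groups shrink: power | Detectable difference | Comparison held at 144: power | Detectable difference |
|---|---|---|---|---|
| 144 | .88 | .45 | .88 | .45 |
| 140 | .87 | .45 | .88 | .45 |
| 115 | .80 | .50 | .84 | .47 |
| 112 | .79 | .51 | .835 | .48 |
| 98 | .73 | .54 | .805 | .50 |
| 96 | .73 | .55 | .80 | .50 |
| 88 | .69 | .57 | .78 | .51 |
| 70 | .59 | .64 | .72 | .55 |

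Taking 140 as the pool, 112, 98 and 70 are 80%, 70% and 50% of it, and 88 is 70% with a further 10% lost. Worked example for 98 against 144: SE = 1.353 × √(1/98 + 1/144) = .177; .50/.177 = 2.82; Φ(2.82 − 1.96) = .805.

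**4. Clustering alone, at full numbers (illustrative).** If the clusters were the former preschools, the average size would be 140/13 = 10.8 and the design effect 1 + 9.8 × ICC. Dividing n by the design effect gives:

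| Assumed ICC | Design effect | PATHS group only | Both groups |
|---|---|---|---|
| .01 | 1.10 | .86 | .85 |
| .02 | 1.20 | .85 | .82 |
| .05 | 1.49 | .80 | .73 |

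**The case against.** Several objections have force.

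- **140 is not an established ceiling.** The inclusion criterion asks that the child took part in the PATHS trial, which can be read to cover former wait-list children. The 144 may also already be the families who agreed to further contact, in which case counting that agreement as another loss would be double counting. Both stand. The count still needs explaining, and fresh consent and loss before T2 still lie ahead.
- **Only the PATHS side is closed.** Comparison families come from a registry recruitment pool, so refusals there may be replaceable. This stands, and is why the table carries both columns. The article does not say that replacement will happen, and matching may limit it.
- **Complete data is an inference.** The simulation description is silent on missing data, and maximum likelihood can use families with T1 only. True, but such families add little about change.
- **The clustering figures are conjecture.** No ICC is given, and the text does not say whether the schools are the former preschools or the children's present schools. This stands. The article may also leave simulation detail to a fuller plan, but here it publishes a figure whose stated inputs omit a feature of the analysis described in the same subsection.
- **Nothing is miscalculated, and the sample size is openly called an assumption.** Agreed. The fault lies in the assumption.

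A reader might infer that the trial has little better than even odds of detecting .50. The documents do not support that. It would take loss of well over half the families in both groups, and no such rate is stated.

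**Conclusion.** The point holds. The .88 describes a trial in which the entire closed PATHS-side pool is analysed, and the article's own eligibility, consent, follow-up and T2 arrangements make that unlikely. Power drops below .80 at fewer than about 115 families per group if both groups shrink, or at fewer than about 96 PATHS families if the comparison group stays at 144; at 70 PATHS families and 144 comparisons it is .72. The conflict between 144 and 140/145 must be reconciled, but it is worth only about one point of power. The clustering omission is real as described; its size is unknown.

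These figures rest on a two-sided .05 level, an SD of change calibrated so that 144 per group gives exactly .88, and illustrative participation levels. Confidence is high that the allowance is missing from the stated calculation, and lower for any particular power value. The stronger claim that the trial is known to be badly underpowered does not follow: no participation rate is given, and full recruitment of comparison families would soften the loss.

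**What to change.** 1. Reconcile 144 with 140 and 145: say which children form the cohort, and whether 144 is already the subset whose parents agreed to further contact.
2. Re-run the Monte Carlo and replace the single .88 with power and detectable difference over a stated range of usable PATHS families, once with the comparison group shrinking equally and once with it held at 144. Recruitment has begun, so the sponsor should be able to say where in the range it expects to land.
3. State the latent slope SD in which the .50 is expressed, so that the figure can be reproduced.
4. Add a sensitivity range for clustering, naming the cluster unit and labelling it and the ICC values as assumptions.

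The cost is a re-run of an existing simulation and a short restatement. The published power becomes less favourable. No extra families are needed.
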